### Participants

52 patients with PD [26 from Winnipeg, MB, Canada (site 1) and 26 from Toronto, ON, Canada (site 2)], and 15 age-matched healthy, able-bodied control subjects (site 1) will be recruited in a 2-year time period. The criteria used for recruitment of the patients will include; (a) diagnosis of PD according to United Kingdom brain bank criteria (Hughes et al., 1992), (b) stage II-III of PD according to the Hoehn and Yahr scale (Bhidayasiri and Tarsy, 2012), (c) age 50–75 years, (d) adequate vision to see required images on a standard computer monitor, (e) able to score 26 or greater on the Montréal cognitive assessment scale [MoCA (Marinus et al., 2011)], (f) on stable medications for the past 3 months, and (g) able to walk overground for 2 min without an aid or cane. The exclusion criteria for participation will include the following: (a) diagnosis of any psychiatric comorbidity or history of any other neurological disease other than PD, (b) any other medical condition limiting participant ability to walk on the treadmill, and (c) neuroimaging contraindications (i.e., claustrophobia, severe dyskinesia, diabetes, non-compatible metal implants, etc.). Healthy able-bodied adults with the same inclusion/exclusion criteria listed above except for diagnosis of PD will be recruited.

All responders to calls for participation will undergo a screening assessment. Ethics approval has been obtained from the institutional Human Research Ethics Boards. All volunteer participants will be asked to read and sign the informed consent form. The Clinical trial has been registered at ClinicalTrials.gov, identifier: NCT04415775.

Successfully screened PD participants will be randomized to the experimental intervention (XG) or an active control arm (CG). A computerized block randomization procedure will be implemented by an independent statistician. Randomization will be stratified by stage of the disease (Hoehn and Yahr stage II and III). To ensure similar representation of men and women, randomization will also be stratified by sex. Randomization will be achieved by having participants choose an opaque sealed envelope, each containing a group assignment.

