### Neuroimaging Equipment

Positron emission tomography images will be acquired using a Siemens Biograph mCT PET/CT scanner (Siemens Healthineers, Knoxville, TN, United States). Participants will be administered 185 MBq of [^18^F] FDG. For participants recruited in Winnipeg, MRI images will be acquired on a 3-Tesla Siemens/IMRIS MAGNETOM Verio MRI scanner (Erlangen, Germany), using a 12-channel head and neck coil. Participants recruited in Toronto will be scanned using a 3-Tesla, GE Discovery MR750 scanner.

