For the neuroimaging data, Aim 1 will use PET data to compare levels of metabolic activity by region between; (a) single-walk only and DT-walk trials, and (b) PD and able-bodied age-matched controls. Aim 2 will use PET and MRI (RS-fMRI, pCASL, and DTI) data to investigate neural changes (whole-brain and ROIs) between pre- and post-intervention. See Table 1 for the ROIs to be used in the PET and RS-fMRI data for Aims 1 and 2. Paired sample *t*-tests will be conducted for these different neuroimaging modalities, with age and gender included as regressors of no interest. Additional correlational analyses are planned to investigate the relationship between changes in neural activity and behavioral metrics such as cognitive task performance and gait measures.

**TABLE 1 T1:** Regions of interest for the PET and fMRI ROI analyses.

**Amygdala, L**	**Dorsolateral PFC, L**	**Inferior Temporal, R**	**Mesial Temporal, L**	**Orbital frontal, R**	**Thalamus, R**
Amygdala, R	Dorsolateral PFC, R	Insula, L	Mesial Temporal, R	Putamen, L	Uncus, L
Anterior Cingulate, L	Frontal pole, L	Insula, R	Midbrain	Putamen, R	Uncus, R
Anterior Cingulate, R	Frontal pole, R	Lateral Temporal, L	Middle Temporal, L	Substantia nigra	Ventral Striatum, L
Subgenual cingulate (BA 25)	Hippocampus, L	Lateral Temporal, R	Middle Temporal, R	Superior Temporal, L	Ventral Striatum, R
Caudate, L	Hippocampus, R	Medial PFC, L	Occipital	Superior Temporal, R	Ventrolateral PFC, L
Caudate, R	Inferior Temporal, L	Medial PFC, R	Orbital frontal, L	Thalamus, L	Ventrolateral PFC, R

*L, left; R, right; PFC, prefrontal cortex.*

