In regards to the pilot MRI data, we expect significant neural changes across modalities. Due to the importance of the dorsolateral PFC for both cognition and gait, we expect both PD groups to have reduced functional connectivity between this region and other basal structures compared to able-bodied controls using RS-fMRI data (Monchi et al., 2004; Nagano-Saito et al., 2014). We expect that following intervention, the XG group will have increased functional connectivity between these regions compared to the CG group, and that this functional connectivity will correlate with PD stage. Similarly, in the whole-brain RS-fMRI analysis, we hypothesize that pre-intervention, both PD groups will have altered functional connectivity within central executive, sensorimotor, visual, default mode, and cerebellar resting state networks compared to healthy controls (de Schipper et al., 2018; Wolters et al., 2019; Dong et al., 2020; Schneider et al., 2020), but that PD groups will not differ from each other. Post-intervention, we hypothesize that functional connectivity within these networks will differ between XG and CG PD groups. For the pilot pCASL data, we hypothesize that SVM-ISDA scores will not differ between PD groups at baseline, but will differ from able-bodied controls. Following intervention, we hypothesize that scores for both XG and CG groups will be reduced, with a larger effect observed for the XG group, indicating a larger treatment response. Although the DTI data are largely pilot data in nature, based on previous research indicating that reduced white matter integrity in forceps minor, corpus callosum, uncinate fasciculus, and cingulum is associated with reduced gait stability and may be associated with an increased risk of falling (Ghanavati et al., 2018; Snir et al., 2019), we hypothesize that the same relationship will hold in our sample. While it is thus far unclear whether structural changes in DTI can be observed in our population following 10-weeks of intervention, we expect that increased white matter integrity at post-intervention will be associated with improved gait stability and reduced number of falls at the 6-month follow-up.

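### The MRI comparisons of Parkinson's patients with healthy controls are partly confounded with scanner, and the stated regressors do not include site

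*Protocol article*

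**What the plan says.** **Who is scanned where.** Under Participants, the 52 PD patients are recruited equally at Winnipeg (site 1) and Toronto (site 2), 26 each. The controls are at site 1 only: "15 age-matched healthy, able-bodied control subjects (site 1) will be recruited in a 2-year time period".

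**On which MRI scanner.** Under Neuroimaging Equipment: "For participants recruited in Winnipeg, MRI images will be acquired on a 3-Tesla Siemens/IMRIS MAGNETOM Verio MRI scanner". For the other site: "Participants recruited in Toronto will be scanned using a 3-Tesla, GE Discovery MR750 scanner".

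**What is compared.** Under Anticipated and Preliminary Results, the authors expect "both PD groups to have reduced functional connectivity between this region and other basal structures compared to able-bodied controls". The same section predicts that both PD groups will differ from controls within five resting-state networks before the intervention, and that baseline pCASL SVM-ISDA scores will differ from controls. RS-fMRI Analyses also plans a between-group comparison of global graph metrics, without naming the groups.

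**With which adjustment.** The neuroimaging paragraph of Statistical Analyses specifies paired t-tests for the imaging modalities "with age and gender included as regressors of no interest". No site or scanner term is listed. The preprocessing and modality-specific analysis sections contain no cross-scanner harmonisation step.

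**The concern.** A PD-versus-control contrast compares different people, so a scanner offset does not cancel as it does in a within-person change. Here 50% of the patients and none of the controls are on the GE scanner. If Siemens and GE give systematically different connectivity or perfusion values, part of that difference will be reported as a PD abnormality, or will mask a real one, depending on its sign.

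The affected statements are the resting-state connectivity and network hypotheses and the pCASL score hypothesis. Specifying the handling in advance matters because a choice between pooled, adjusted and site-1-only results made after seeing the data leaves the analyst free to pick.

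**Working it through.** **Inputs from the article.** PD at site 1: 26. PD at site 2: 26. Controls at site 1: 15. Controls at site 2: 0. Significance level 0.05 (sidedness not stated; two-sided assumed).

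**Input assumed.** An additive scanner offset of s SD on the GE scanner. The article gives no value, so s is varied from 0.2 to 1.0. Outcomes are taken as normal with equal variance. The article has no figure of its own on this point to reproduce.

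**Step 1: bias of the pooled contrast.** With no true disease effect, the expected PD mean is (26 × 0 + 26 × s)/52 = 0.5s and the expected control mean is 0. The unadjusted difference is therefore biased by 0.5s.

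**Step 2: standard errors.**
- Pooled, no site term: √(1/52 + 1/15) = 0.293 SD.
- Site 1 only, or all 52 with a site term: √(1/26 + 1/15) = 0.324 SD.
- Ratio: 0.324/0.293 = 1.106, so about 11% wider.

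The last two share a standard error because no controls are at site 2. The site term absorbs the Toronto patients' mean, and the disease contrast becomes Winnipeg patients minus controls. Toronto then contributes only to the residual variance.

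**Step 3: false-positive rate.** Simulated t-tests of 52 versus 15 under a true null (100,000 data sets per setting):

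| Assumed s (SD) | Bias 0.5s (SD) | Pooled, equal-variance t | Pooled, Welch t | Site 1 only |
|---|---|---|---|---|
| 0.2 | 0.10 | 6% | 6% | 5% |
| 0.5 | 0.25 | 12% | 13% | 5% |
| 0.8 | 0.40 | 23% | 25% | 5% |
| 1.0 | 0.50 | 32% | 35–36% | 5% |

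The model with a site term also holds about 5% throughout.

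**Step 4: power cost of the remedy.** Pooled unadjusted power (taking s = 0) against power with a site term, two-sided 5%:

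| True difference (SD) | Pooled, unadjusted | With site term |
|---|---|---|
| 0.5 | 39% | 33% |
| 0.8 | 77% | 68% |
| 1.0 | 92% | 86% |

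Restricting to site 1 costs slightly more because there are fewer residual degrees of freedom: 67% at 0.8 SD.

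**The case against.** **The covariate sentence concerns paired tests.** Age and gender are attached to paired t-tests, which are within-person, and no two-sample MRI model of 52 against 15 is written out. This is right as far as it goes: the pooled unadjusted test is an inference. But the same paragraph includes a PD-versus-control comparison, which cannot be paired. The list is the only one given for imaging, and the hypotheses refer to both PD groups, drawn from both sites. Pooling with age and gender alone is the natural reading.

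**A condensed article may leave site handling to an analysis plan that is not shown.** Silence alone would not be a finding. Here the article names its regressors, and site is not among them.

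**The MRI data are pilot.** The Introduction and Anticipated and Preliminary Results both say so, and the neuroimaging paragraph assigns MRI to pre-versus-post change. This stands and lowers the severity.

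**Stronger readings that the documents do not support.**
- *That the formal PD-versus-control comparison is confounded with scanner.* It is a PET comparison: "Aim 1 will use PET data to compare levels of metabolic activity by region between". One scanner model is named for it: "Positron emission tomography images will be acquired using a Siemens Biograph mCT PET/CT scanner". Images are scaled to their global value, and the text shows no PET scanner difference between sites. Controls still come from one site only, but the MRI argument does not carry over.
- *That XG versus CG is biased.* Assignment is randomised, sample size is planned per group and site, and a constant offset cancels in a patient's pre-post change if that patient stays on one scanner. Omitting site costs precision at most.
- *That the offset cannot be separated from disease.* It can. There are 26 PD patients on each scanner, and 26 share the controls' scanner.

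**Conclusion.** The point holds for the MRI contrasts between PD patients and controls: RS-fMRI connectivity and networks, and pCASL SVM-ISDA scores. These are partly confounded with scanner, and the stated regressors do not remove it. The bias is half of whatever offset exists. Over assumed offsets of 0.2 to 1.0 SD, a nominal 5% test has a true error rate of about 6% to 32–36%.

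The 0.5 factor follows from the planned numbers and would shift somewhat with unequal recruitment or dropout. The error rates depend on the assumed offset, on its being additive, and on pooling without a site term. If the two scanners agree closely, little is lost.

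This is a cheap improvement, not a must-fix, because the contrasts are pilot and the bias can be removed with data already planned.

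**What to change.** State in the neuroimaging part of Statistical Analyses that every MRI comparison of PD patients with controls uses the 26 Winnipeg patients and the 15 controls, or carries a site/scanner term when all 52 patients are included. Say which of the two is the main analysis. Apply the rule to the graph metrics as well, if the groups meant there include controls.

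The cost is a change of wording, with no extra scans or participants. The standard error rises by about 11% (0.293 to 0.324 SD), and power at a difference of 0.8 SD falls from 77% to 68% with a site term.

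Optionally, add site as a covariate to the XG-versus-CG models. That may gain precision but is not needed to correct bias. The scanner argument calls for no change to the PET comparison.

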### Test Procedures and Protocols

#### Intervention Protocol

The experimental timeline is visualized in Figure 1. All PD participants will undergo a 10-week exercise program, three times per week. Each therapy session will involve: (a) 10-min warm-up of balance exercises while standing on a sponge or balance disk, and (b) treadmill-walking of 3- to 5-min intervals and with 1-min rest periods for a total duration of 35 min. The type of compliant surface used, and the treadmill speed will be adjusted so that participants will not require the use of the handrails or any other body support. As with the gait assessments participants will be fitted with a body harness connected to a LiteGait support structure.

**FIGURE 1 F1:**
[figure not shown]
Experimental timeline. Assessment days (ADay) indicate order of assessments. PET scans on ADay_3_ and ADay_4_ will be counterbalanced between a single-task treadmill walking only task and a DT treadmill walking and cognitive game condition. A final DT PET scan will be acquired following intervention (ADay_7_). MRI scans will be collected pre- (ADay_2_) and post-intervention (ADay_6_). Behavioral testing (Behav; including motor measures and neuropsychological testing) will occur on three occasions: prior to intervention (ADay_1_), following intervention (ADay_5_), and again after a 6-month follow-up. Fall-history and physical activity tracking will be acquired throughout, until 12-months post-intervention. Measures of gait will be acquired throughout the program, including during behavioral assessment days, at each training session, and on PET assessment days. The experimental (XG) and control arm (CG) groups will complete the entire timeline, while healthy controls (HC) will complete up until ADay_4_.

Participants in the CG group will complete 10 weeks of a “single-task” exercise program including videogames only (i.e., for 10 min while sitting) and walking-only on the treadmill—these tasks are conducted independently, one at a time. Participants in the XG will perform various cognitive computer games during the warm up period on the compliant surface and during all treadmill walking intervals. The computer games will be played using the head mounted IB-mouse as described above. Many inexpensive and easily accessible common and modern games exist which are visually rich, fun, and engaging. They include a variety of tasks that require; (i) visual search and tracking of multiple targets, (ii) speed accuracy requirements, (iii) presence of distracters, (iv) matching tasks, and (v) working memory. Note that the games that will be used during behavioral and PET assessments and those used in the XG exercise program are different.

As in most physical therapy programs, the specifics of DT training are customized for each patient, and the program gradually becomes more challenging as a patient’s performance improves. In the first DT training meeting, 6–10 games will be selected for each participant for their 10-week training session. They will be selected according to the domains of executive function, and also the personal preferences of the participant. Each game has hundreds of difficulty levels and as each level is successfully completed then the game automatically advances to the next difficulty level. Some games are less difficult than others, i.e., starting difficulty level can be easy, moderate, or hard. Thus, different games can be chosen to progress the difficulty level of the mental activities, i.e., speed of play, precision level, movement amplitudes, and distractions. Physical demands (i.e., type, thickness, and density of the compliant surface and the treadmill speed) will be progressed as tolerated. Participants in the CG group will be asked to play the computer video games using the IB-mouse while sitting for 10 min prior to treadmill walking. This will allow the CG group to have adequate practice using head rotation to control the IB-mouse which is used for assessment of DT performance.

#### Behavioral Testing

Behavioral testing includes motor and gait assessment and neuropsychological testing (described below). Behavioral testing will occur prior to intervention at baseline, immediately following intervention, and at a 6-month follow-up (see Figure 1). Gait measurements will be conducted throughout the duration of the experiment to track participant progress; however, it is important to note that these gait variables are in addition to those gathered under the more stringent assessment sessions. Additionally, physical activity tracking will take place continuously and will be acquired for 12 months following treatment.

##### Motor and Gait Assessment

Behavioral assessment of each PD participant will be conducted on three occasions, before and after a 10-week exercise program, and at a 6-month follow-up time period. Healthy control participants will be assessed at time 1 only. PD participants will initially be assessed with the Part-III (motor) section of the Movement Disorder Society—Unified Parkinson Disease Rating Scale [MDS-UPDRS (Goetz et al., 2008)]. Assessment of gait function under single-task (walk only) and DT conditions will be conducted on a treadmill, instrumented with a pressure mapping system. Treadmill walking is used to obtain 40–60 consecutive steps and at a constant speed [see Bhatt (2018) and Szturm et al. (2017) for a detailed description of data recording, analysis, and test-retest reliability]. Participants will be instructed to walk on the treadmill at their preferred gait speed without hand support for four 1-min intervals (one single-task walking only, one VMT, and two VCG trials, described below). The center-of-pressure of foot displacement in the mediolateral (ML) and anteroposterior (AP) directions will be collected at 100 Hz.

A custom computer application with the following two assessment modules will be used for the DT test conditions: (a) a visuomotor tracking (VMT) task and (b) a visuospatial cognitive game (VCG) task. Figure 2 illustrates the gaming set-up for the VMT and VCG tasks. As described previously (Nankar et al., 2017; Szturm et al., 2017; Ahmadi et al., 2019; Mahana et al., 2021), an IB-mouse will be used to control and interact with the cognitive assessment games. The VMT task used in the present study requires real-time, on-line visual feedback of the relative positions of two objects. The VCG task requires visual search to locate target objects and cognitive inhibition to avoid distractors. The VMT and VCG tasks require precision head-pointing movement. Many real-life tasks involve head movements to track and locate various objects, and for information processing of what are being seen. The increased visuospatial processing necessary to maintain walking rhythm and to correct for any drifting on the treadmill would compete for resources required to perform the VMT and VCG tasks, and vice versa.

**FIGURE 2 F2:**
[figure not shown]
Illustration of the DT gaming set-up and snapshots of the visuomotor tracking (VMT, panel **A**) and visuospatial cognitive games (VCG, panel **C**). Panel **(B)** shows a participant wearing a plastic headband with inertial motion mouse. The goal of the VMT game is to track and overlap the game paddle (rectangle object) with a moving circle object (computer controlled). The goal of the VCG is to move the game paddle, catch target objects (soccer ball), and avoid distractors (dotted sphere). Panel **(D)** plot shows typical movement trajectory of a healthy young adult playing the game. Panel **(E)** presents a single game movement trajectory (game paddle coordinates) of one game event from target appearance (time zero) to target disappearance (time 2s). All segmented game movement trajectories of one game session are sorted and grouped by direction. Panel **(F)** presents overlay plots of the segmented and sorted game movement trajectories for a 60 s game trial. Presented are the game movement trajectories for rightward head rotations. Details on how to quantitate behavioral output measures have been published elsewhere (Nankar et al., 2017; Szturm et al., 2017; Ahmadi et al., 2019).

A treadmill was chosen for the DT gait and cognitive functions for the following reasons. First, treadmill walking was chosen to overcome the confounding effect of gait speed. The treadmill allows the speed to be kept constant between walking conditions (single-task and DT), and over repeated measures (pre- and post-intervention time periods). This is of particular importance to standardize the uptake period of the PET imaging analysis at the three test periods. Most DT gait studies are performed overground, and all overground studies report a significant decrease in gait speed during the DT-walking condition, as compared to walk-only trials (Stegemöller et al., 2014; Raffegeau et al., 2019). Therefore, during overground DT-walking trials, there is a planned strategy to reduce the physical demands or threat to balance. Besides gait speed, many DT gait studies examine how cognitive demands affect gait rhythm and stability [i.e., recording spatiotemporal gait variables or analysis of trunk linear acceleration (Ijmker and Lamoth, 2012; Montero-Odasso et al., 2012; Asai et al., 2013; Martinez-Martin et al., 2013; Nankar et al., 2017; Ahmadi et al., 2019)]. However, gait speed is a confounding variable, as spatiotemporal gait variables and trunk acceleration are sensitive to changes in gait speed (Frenkel-Toledo et al., 2005; Jordan et al., 2007; Kang and Dingwell, 2008; Keene et al., 2016; Cole et al., 2017). Most overground DT-walking studies use an instrumented walkway, which records only 4–6 consecutive steps. It has been shown that using a continuous walking protocol, instead of short intermittent walks, and collecting more than 30 consecutive steps improved reliability, in particular for measures of gait variability and during DT-walking trials (Bruijn et al., 2009; Hollman et al., 2010; Galna et al., 2013). In addition, there is a limited choice of executive cognitive tasks that can be assessed during the short time period to walk a few meters. For example, cognitive tasks used during overground walking include walking while talking, recall of names/words, serial subtraction, or auditory Stroop (Stegemöller et al., 2014; Gregory et al., 2017; Ghanavati et al., 2018; Raffegeau et al., 2019; Snir et al., 2019). The present study extends these assessments to include visuomotor and visuospatial cognitive tasks assessed over a 1-min time period. Tracking visual objects and processing of what is being seen are important cognitive functions to consider in the analysis of DT interference on mobility (Nagamatsu et al., 2009; Logan et al., 2010). Cortical areas devoted to visual spatial ability such as the frontal and parietal lobes may be particularly susceptible to the neurodegenerative process of PD (Battisto et al., 2018; Lally et al., 2020). Following the principle of neural overlap (Crockett et al., 2017), DT interference should be greatest when the cognitive and motor tasks engage the same neural circuits and processing resources, e.g., visual-spatial processing. Walking endurance will be evaluated with a 6-min walk test [6MWT (Combs et al., 2014)]. Overground walking speed will also be evaluated over 25 m in a straight corridor.
